## Abstract

**Introduction:**

Endometriosis is a chronic disease that affects up to 190 million women and those assigned female at birth and remains unresolved mainly in terms of etiology and optimal therapy. It is defined by the presence of endometrium-like tissue outside the uterine cavity and is commonly associated with chronic pelvic pain, infertility, and decreased quality of life. Despite the availability of various screening methods (e.g., biomarkers, genomic analysis, imaging techniques) intended to replace the need for invasive surgery, the time to diagnosis remains in the range of 4 to 11 years.

**Aims:**

This study aims to create a large prospective data bank using the Lucy mobile health application (Lucy app) and analyze patient profiles and structured clinical data. In addition, we will investigate the association of removed or restricted dietary components with quality of life, pain, and central pain sensitization.

**Methods:**

A baseline and a longitudinal questionnaire in the Lucy app collects real-world, self-reported information on symptoms of endometriosis, socio-demographics, mental and physical health, economic factors, nutritional, and other lifestyle factors. 5,000 women with confirmed endometriosis and 5,000 women without diagnosed endometriosis in a control group will be enrolled and followed up for one year. With this information, any connections between recorded symptoms and endometriosis will be analyzed using machine learning.

**Conclusions:**

We aim to develop a phenotypic description of women with endometriosis by linking the collected data with existing registry-based information on endometriosis diagnosis, healthcare utilization, and big data approach. This may help to achieve earlier detection of endometriosis with pelvic pain and significantly reduce the current diagnostic delay. Additionally, we may identify dietary components that worsen the quality of life and pain in women with endometriosis, upon which we can create real-world data-based nutritional recommendations.

## Introduction

Endometriosis is a chronic inflammatory disease with endometrium-like tissue outside the uterine cavity [1, 2]. It is commonly associated with chronic pelvic pain, infertility, and decreased quality of life, although asymptomatic cases exist [3–5]. The exact prevalence of endometriosis is unknown, but it may affect 5–10% of women and those assigned female at birth during their reproductive years, which equals nearly 190 million people worldwide [1]. Despite this high prevalence, recognition of the disease is inadequate, underprioritized, and research is underfunded, contributing to diagnostic delays ranging from 4 to 11 years [6–9]. Accordingly, endometriosis should be considered a public health issue, and reducing the current diagnostic delay is paramount.

Lucy is a mobile health application (Lucy app) designed to alert users with an increased risk of endometriosis to seek medical attention. Users can input their menstrual cycle information, health status, medical records or diagnoses, dietary details, lifestyle, and pain symptoms. Specialists in reproductive gynecology and health psychologists developed the app’s algorithm to continuously analyze the recorded data and alert the user when the entered symptoms are strongly associated with endometriosis.

A baseline questionnaire and a longitudinal questionnaire were developed and implemented as an additional module in the Lucy app. It collects self-reported data on symptoms of endometriosis, socio-demographics, mental and physical health, economic factors, nutrition, and other lifestyle factors [10]. By linking the collected information with existing registry-based information on diagnoses of endometriosis, healthcare use, and the big data approach, we can develop a phenotype description of individuals with endometriosis and structured clinical data [11].

So far, only one study has investigated this question with big data analysis using machine learning (ML). According to Bendifallah *et al*., endometriosis can generally be diagnosed with high diagnostic accuracy based on endometriosis-related symptoms and demographic data using ML technology [12]. The work presented by these authors was based on medical records of 800 participants of a French cohort and not on patient self-reported data.

No evidence-based advice concerning effective dietary interventions can be given to women with endometriosis [13]. Specifically, the effect of red meat, sugar, soy, dairy products, gluten, and caffeine on symptoms in women with endometriosis has not yet been systematically recorded. Therefore, we aim to investigate the effects of dietary restriction of these components on changes in quality of life, pain, and central pain sensitization. With this information, we may be able to identify nutritional components that affect the quality of life and pain in women with endometriosis. Consequently, real-world data-based dietary recommendations could be generated.

The present study aims to investigate the association between self-reported data and the clinical presentation of endometriosis. This could contribute to the classification of novel etiologic endometriosis. Such etiological findings could help to identify patterns that may categorize novel clinical subgroups of the disease. In addition, developing patient profiles may provide a novel diagnostic tool for the non-invasive, early detection of endometriosis.

### Who would benefit from the early diagnosis of the disease?

In patients with negative imaging, the definitive diagnosis of endometriosis is still laparoscopic intervention and histological analysis, which requires invasive evaluation and direct visualization of lesions, followed by histological analysis [6]. To initiate treatment, including surgery, we need a clinical hypothesis based on signs and symptoms of endometriosis, which can lead to a late diagnosis of the disease. Due to the lack of non-invasive diagnostic tools, the average delay in diagnosing endometriosis from the onset of the symptoms is 11.7 years in the United States, 8 years in the United Kingdom, and 3.9 years in Hungary [14, 15]. A non-invasive diagnostic tool would be crucial in early endometriosis diagnosis, especially the minimal-mild (#Enzian P, ASRM Stage I-II) endometriosis [16, 17].

## Objectives

### Primary objective

To establish a comprehensive real-world big data repository using the *Lucy app*. This initiative aims to identify unique clinical cohorts by leveraging various factors such as digital footprints, symptoms, patient experience, comorbidities, clinical severity, and lifestyle patterns. Using ML for big data analytics, patient profiles and structured clinical data that facilitate the earlier detection of endometriosis can be generated. Ultimately, this approach has the potential to reduce the current diagnostic delay associated with endometriosis significantly.

### Secondary objectives

To explore whether there is an association between removing or restricting dietary components and quality of life, pain, and central sensitization.To investigate the connections between different types of exercise, relaxation techniques, and the symptoms or diagnosis of individuals.To measure the financial implications of specific diets and different dietary supplements.

## Materials and methods

### Ethics statement

This non-interventional study protocol was approved by the ethics committee of the Medical Research Council of Hungary and authorized by the National Institute of Pharmacy and Nutrition of Hungary (OGYÉI/31355/2021). It is conducted following the tenets of the Declaration of Helsinki. Before completing the questionnaires for the first time, participants will receive an informational briefing detailing the nature of the research. The application necessitates accepting the privacy policy and informational disclosure, explicitly stating that their data may be used for research purposes. The data controller only stores aggregated, anonymous data from the data provided in the *Lucy app* and the use of the application. See https://hellolucy.app/hu/protection and https://hellolucy.app/hu/agreement for detailed information.

### Study design

This study is conducted as a multicenter, parallel-group trial. Study participants are being recruited through the Lucy app. Data are collected in the following countries: Hungary, Denmark, Sweden, Germany, Austria, Italy, Romania, and Poland. Participant recruitment began on 08 February 2022 and is expected to continue until 31 December 2024.

### Eligibility criteria

5,000 women with confirmed endometriosis and 5,000 women without diagnosed endometriosis in a control group aged 18–45 years will be enrolled and followed up for one year.

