### Exclusion criteria

The following exclusion criteria have been defined:

Ongoing pregnancy.Lactation.Concern for pre-malignancy or presence/history of malignancy.

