### Statistical and machine learning analyses

Our dataset comprises both diagnosed and undiagnosed patients, enabling us to evaluate the quality of the data. The goal is to have a case-control ratio of 1:1 in the dataset. Specifically, records from patients diagnosed with endometriosis but not yet received treatment should highly correlate with well-known endometriosis-associated symptoms, such as pelvic pain.

The normal distribution of the data will be tested with histograms and QQ-plots. Continuous variables will be presented as averages (mean ± SD), nominal variables as numbers (n) and percentages (%). A level of statistical significance of P < 0.05 will be used. The VAS scores of the endometriosis group and the reference group will be compared with independent sample t-tests. Also, independent samples t-tests will be conducted to see whether EQ-5D-5L, CSI-9 and EHP-5 scores were different between diet-users and non-diet users. Subsequently, a one-way analysis of variance of no diet use and the various diets will be carried out for the EQ-5D-5L, CSI-9, and EHP-5 scores. A post-hoc multiple comparisons analysis (Tukey honestly significant difference) will be used to identify where the differences between these diet groups were located. Preliminary analyses will involve various correlation techniques and visual representations, including heat maps contrasting diseases against symptoms.

To explore associations between diseases, symptoms, severity, dietary habits, and lifestyle activities, we will employ Cramér’s V statistical method. Additional validation of patient segmentation will be conducted to confirm that emerging patient cohorts exhibit anticipated symptoms. Machine learning algorithms will be deployed to uncover hidden relationships or patterns. Density-Based Spatial Clustering of Applications with Noise (DBSCAN) and Uniform Manifold Approximation and Projection (UMAP) will be employed to visualize high-dimensional symptom and activity spaces in 2D or 3D representations for dimensionality reduction and clustering. Risk assessments for undiagnosed patients will be computed using Random Forest and Long Short-Term Memory (LSTM) models. The LSTM models will fully leverage the time-series data, offering predictive insights into disease outcomes based on the temporal progression of symptoms.

All the methodologies above will be tested under various scenarios, such as:

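### The abstract claims earlier detection of endometriosis with pelvic pain, but no listed model test is confined to women with pelvic pain, so whole-cohort discrimination may overstate performance for that claim

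*Protocol article*

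**What the plan says.** The intended use appears in two places. The abstract's conclusions say: "This may help to achieve earlier detection of endometriosis with pelvic pain and significantly reduce the current diagnostic delay". The section on who would benefit from early diagnosis adds early disease: "A non-invasive diagnostic tool would be crucial in early endometriosis diagnosis, especially the minimal-mild (#Enzian P, ASRM Stage I-II) endometriosis".

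The comparison groups are fixed under Eligibility criteria: "5,000 women with confirmed endometriosis and 5,000 women without diagnosed endometriosis in a control group aged 18–45 years will be enrolled". The only exclusions are "Ongoing pregnancy.Lactation.Concern for pre-malignancy or presence/history of malignancy". On the source of participants, Study design states: "Study participants are being recruited through the Lucy app". The analysis section adds: "The goal is to have a case-control ratio of 1:1 in the dataset". Pelvic pain, clinical suspicion and disease stage are not criteria for either group.

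For the prediction models, Statistical and machine learning analyses says: "Risk assessments for undiagnosed patients will be computed using Random Forest and Long Short-Term Memory (LSTM) models". It then gives examples of scenarios under which the methods will be tested: using all symptom and lifestyle variables, dropping variables that the literature suggests are irrelevant, and splitting diagnosed from undiagnosed women. The article expects these tests to show whether results are consistent and reliable. The same section expects pelvic pain to be a strong marker of diagnosed but untreated women, and plans a t-test of VAS pain between the endometriosis and reference groups.

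**The concern.** A model's discrimination depends on who is compared with whom. If cases report pelvic pain more often than controls, the presence of pain separates the groups and raises the whole-cohort AUC. Among women who all have pelvic pain, that yes/no item is constant and contributes nothing. A good whole-cohort figure could then be read as support for the pelvic-pain statement in the abstract when much of it came from a contrast that is absent in those women.

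The listed scenarios would not reveal this. The first two change the variables and leave the women the same. The third splits on the outcome label, so discrimination between cases and controls cannot be assessed inside either segment. Correct labels, or balance on age and country, would not remove the problem, because it concerns the mix of symptoms in the two groups.

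At stake is what the study may conclude about detecting endometriosis in women with pelvic pain, and so about shortening their diagnostic delay.

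**Working it through.** **The plan's own figure.** The targets of 5,000 and 5,000 agree with the 1:1 goal (5,000/5,000 = 1). The article gives no pain prevalence, AUC, sensitivity, specificity or stage mix. Everything below is therefore illustration under stated assumptions.

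**Step 1: pain as a yes/no item alone.** AUC = 0.5 + (P(pain in cases) − P(pain in controls))/2.
- 80% v 30%: 0.5 + 0.50/2 = 0.75
- 90% v 20%: 0.5 + 0.70/2 = 0.85
- 70% v 60%: 0.5 + 0.10/2 = 0.55
- Everyone has pain: 0.5 + 0/2 = 0.50

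**Step 2: pain plus all other items.** The other items are summarised as one normal score, independent of pain within each group, with mean d in cases, 0 in controls and SD 1. If their AUC among women with pain is w, then d = √2 × z(w), where z is the standard normal quantile. For w = 0.65, d = 1.414 × 0.385 = 0.545. The two parts are combined by summing log-likelihood ratios, and the AUC was simulated with 200,000 women per group.

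| Pain, cases/controls | Whole-cohort AUC | AUC among women with pain | Difference |
|---|---|---|---|
| 70% / 70% | 0.651 | 0.65 | about 0 |
| 70% / 60% | 0.661 | 0.65 | 0.01 |
| 70% / 40% | 0.721 | 0.65 | 0.07 |
| 80% / 30% | 0.807 | 0.65 | 0.16 |
| 90% / 20% | 0.889 | 0.65 | 0.24 |

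**Step 3: sensitivity to the assumed 0.65.** At 80%/30%, w = 0.55 gives 0.770 overall, a difference of 0.22. With w = 0.75 the overall AUC is 0.850, a difference of 0.10. The more the other items tell, the smaller the overstatement.

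**Step 4: a force in the other direction.** If a fraction c of controls has undiagnosed endometriosis, the observed AUC is (1 − c) × AUC + 0.5c. Taking the Introduction's 5–10% prevalence as a proxy for c, a true 0.80 becomes 0.95 × 0.80 + 0.025 = 0.785, or 0.90 × 0.80 + 0.05 = 0.77. This lowers the whole-cohort figure slightly.

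**Step 5: stage.** No stage mix is given, so the corresponding effect for Stage I-II disease cannot be put in numbers.

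**The case against.** The strongest reply is that the tool is not only for women with pelvic pain. The Introduction describes an app that alerts users at increased risk, the primary objective speaks of earlier detection without a pain condition, and the models score undiagnosed users in general. For that use, unselected app users are close to the right comparison group and the presence of pain is legitimate information. This stands. It is why whole-cohort performance should be kept, and why the restricted result should not replace it.

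A reader might go further and infer that discrimination will mostly amount to having pain or not, that performance will certainly be overstated, or that the design picks the extremes of disease and health. The documents support none of these. The criteria select neither severe cases nor pain-free controls. No pain prevalence is given, and users of an app meant to flag endometriosis may often have pain themselves. At 70%/70% the gap vanishes. Cases whose pain has been treated, and undiagnosed disease among controls, would lower apparent discrimination. Nor does pain become uninformative once everyone has it: the Questionnaire section collects VAS scores and monthly reports, and the LSTM models use change over time, so intensity and timing can still discriminate.

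Finally, the scenario list is given as examples, the article names no accuracy measure or evaluation population, and a fuller protocol or analysis plan may contain a pain-restricted evaluation. Absence alone would therefore be no fault. What remains is a mismatch within the article: it states a pelvic-pain claim, fixes groups without regard to pain, and offers validation scenarios that do not test that claim.

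**Conclusion.** The point holds in conditional form. Whole-cohort discrimination may overstate performance in women with pelvic pain, and on its own it cannot support the abstract's statement about detecting endometriosis with pelvic pain. With other items at AUC 0.65, the illustrative overstatement runs from about 0 to 0.24, depending almost entirely on how much commoner pain is in cases. The direction rests on pain being commoner in cases, which the article itself expects for untreated cases. The size rests on assumed prevalences and on independence of pain from the other items within each group. For early-stage disease the same reasoning applies, but no size can be given. This is a worthwhile improvement, not an error that invalidates the design.

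**What to change.** Add to the scenarios in Statistical and machine learning analyses an evaluation of the Random Forest and LSTM models restricted to cases and controls who report pelvic pain at baseline. Report it beside the whole-cohort result, which remains the relevant figure for the general app-user alert. Base any statement about detecting endometriosis with pelvic pain on the restricted result. If stage is recorded, also report sensitivity in Stage I-II cases.

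The cost is a change of analysis wording, since symptoms and pain VAS are already collected. There are three downsides:
- **Fewer women.** If 30% of controls have pain (assumed), 0.30 × 5,000 = 1,500 controls remain, so intervals are wider, and the AUC may be less favourable.
- **Selection of cases.** Women whose pain was relieved by treatment drop out of the subset. State this as a limitation.
- **Hidden disease among controls with pain.** It may be concentrated there. If 10% of controls are undiagnosed cases and 80% of those have pain, they make up 0.10 × 0.80/0.30 = 27% of the controls with pain, and an AUC of 0.65 would be observed as 0.73 × 0.65 + 0.27 × 0.5 = 0.61. The report should say that the restricted figure may be low for this reason.

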### Exclusion criteria

The following exclusion criteria have been defined:

Ongoing pregnancy.Lactation.Concern for pre-malignancy or presence/history of malignancy.

### Questionnaire

Participants will be asked to complete a baseline questionnaire once and a longitudinal questionnaire monthly for one year. The questionnaire includes questions about endometriosis symptoms, socio-demographic information, mental and physical health, known medical conditions, medication use, dietary habits, economic burden, and lifestyle factors. These include free-text responses, single or multiple-choice questions, and numerical rating scales. See Supplementary Data for the questionnaires and https://hellolucy.app/en/ for the Lucy app.

Self-reported data of the participants will be measured as follows:

Evaluating the quality of life using the 5-level EQ-5D (EQ-5D-5L) and Endometriosis Health Profile 5 (EHP-5) [18].Assessing pain scores using the Visual Analogue Scale (VAS) [19].Examining somatic and emotional symptoms associated with central pain sensitization using the short version of the Central Sensitization Inventory (CSI-9) [20].

If using the same user account, Lucy app users can pause and resume completing the questionnaire, even on different devices. Once all questions have been answered, users can review and modify their answers on a summary screen. When they submit the questionnaire, their responses are stored on a server. At this point, the questionnaire’s content is fixed and cannot be changed.

In longitudinal studies, minimizing the drop-out rate and encouraging maximum user participation in completing the desired quantity of questionnaires is crucial. *Lucy app* users are anonymous; therefore, personal email contact is impossible. To address this challenge and reduce dropouts, the application uses several methods to notify users when the questionnaire becomes available for completion again. The questionnaire menu is prominently displayed on the application’s main page, and a pop-up window alerts users that the questionnaire is complete. Users can track the number of times and when they completed the questionnaire, but detailed completion data is not visible. The app displays a pop-up window with motivational quotes and positive messages to encourage and support users. In addition, users who complete the questionnaire are entered into a drawing as an additional incentive to participate. These measures are designed to minimize dropout and maximize user engagement in completing the questionnaires for the study.

### Data quality assessment and preprocessing

Given that real-world data inevitably contain inaccuracies, inconsistencies, text inputs, and non-qualitative information, the initial phase of our analysis is dedicated to data quality assessment and filtering. Various data quality metrics will be used, such as confirming the expected data types for each column. We will exclude records with invalid activity dates, missing activity information, users with implausible ages, and a low frequency of activity records. Statistical evaluations will be performed to assess the general data quality. For instance, the distribution of records across different days of the month should be consistent, without significant drop-offs on specific days such as the 31st. The data quality assessment metrics will understand the validity, integrity, precision, reliability, and timeliness of the data to ensure that the primary and secondary objectives can be met with the collected data. After initial filtering, we’ll dive deeper into removing non-qualitative or irrelevant data. Each symptom will be analyzed in terms of its absolute frequency and temporal distribution. Symptoms with sparse records will be discarded to prevent statistical anomalies. Any symptoms showing unrealistic temporal distributions will be subject to medical review to ensure the data’s authenticity.

